#### Follow-up procedure

Follow-up will be made on a regular basis during a 56-day period.

Patients will be called by a research assistant on days 7 and 14 to screen for side effects using the ASEC scale. If any adverse event is screened a clinical opinion will be sought for dose adaptation based on predefined criteria. On day 14, escalation of dose will be prescribed by the PI if symptoms are still under controlled (the corresponding ESAS12-F subscale rated over 3) and in the absence of limiting side effect evaluated using the ASEC and Common Terminology Criteria for Adverse Events V4.0.

Clinical assessment will occur on day 28 (more or less 3 days). This assessment is meant to be made physically; however, if the patients’ condition of public-health situation demands it, it will be performed using teleconsultation. During this consultation, the patient will fulfil the EORTC QLQ-C30, ESAS -12F, HADS-D, and ASEC questionnaires. The PI will weigh the participant, count the number of pills that remains to the patient, evaluate the Performance Status and fill the MARDS. Considering all available data (tolerance, side-effects and symptom control), the PI will make the decision regarding the escalation of treatment dose.

During the final evaluation, on day 56, the patient will fulfil the EORTC QLQ-C30, ESAS -12F, HADS-D, ASEC, and factor 1 of the Medication Adherence Rating Scale (MARS) questionnaires. The PI will weigh the participant, count the number of pills that remains to the patient, evaluate the Performance Status and fill the MADRS.

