***Actions***						
***Inclusion and non-inclusion criteria***	*X*	*X*				
***ECG et postural hypotension test***		*X*				
***Study information delivery***	*X*	*X*				
***Informed consent***		*X*				
***MADRS***	*X*	*(X)*^b^			*X*	*X*
***HADS-D***	*X*	*(X)*^b^			*X*	*X*
***QLQ-C30***		*X*			*X*	*X*
***ESAS12-F***		*X*			*X*	*X*
***ASEC***		*X*	*X*	*X*	*X*	*X*
***Factor 1 of the MARS***					*X*	*X*
***Clinical assessment: weight, blood pressure, Performans Status***		*X*			*X*	*X*
***Treatment list***		*X*			*X*	*X*
***Sociodemographic data***^a^		*X*				
***Randomisation***		*X*				
***Treatment doses adaptation***		*X*	*(X)*	*X*	*X*	*X*
***Adhesion to treatment assessment (pill count)***					*X*	*X*
***Semi-structured interviews***		*X*				*X*
***Side effects***		*X*	*X*	*X*	*X*	*X*

^a^***Socio-demographics:**** date of birth, marital status, number of children, declared level of autonomy/dependence, professional position, way of life, kind of home support, cancer type, stage of the cancer, prior and current cancer treatments, personal background of psychotropic drugs use, the existence of a psychological or nutritional follow-up (and frequency of it)*

^b^***HADS-D/MADRS:**** if not available at the time of screening or older than 7 days old*

^c^***Clinical assessment:**** might be performed using teleconsultation if needed*

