### Inclusion and non-inclusion criteria

Inclusion and non-inclusion criteria are summarized in Table 2.

**Table 2 Tab2:** Inclusion and non-inclusion criteria

Inclusion criteria	Non-inclusion criteria
Being over 18 years old	Being treated with an antidepressant agent during the four weeks before inclusion
Suffering from an advanced cancer	Having had a hypersensivity event to mirtazapine, escitalopram of any excipient
Having a clinically estimated life expectancy over 3 months	Having had a prior inefficient treatment with mirtazapine or escitalopram
	Having postural hypotension or arterial systolic hypotension inferior to 90 mmHg measured following the guidelines of the European Society of Cardiology
Being diagnosed from having a depressive syndrome by a Hospital Anxiety and Depression Scale-D over 11	Having a QT interval over 420 ms
	Having uncontrolled heart rhythm disorder or uncontrolled conduction disorder
Being in need of an antidepressant treatment	Having had or having bipolar disorder
Suffering from at least one under-controlled symptom (defined as a score over 3 on the Edmonton Symptom Assessment Scale) among: pain, nausea, vomiting, breathlessness, lack of appetite, sleep disorders, or anxiety	Having uncontrolled seizure or epilepsy (relative non-inclusion criteria needing a neurology specialist opinion)
	Having or having a history of closed-angle glaucoma
Having or not a cancer treatment	Having bone marrow aplasia
Being able to understand the information related to the study, and to sign informed consent	Practicing breastfeeding or being pregnant
Having agreed to take part in the study	Women of childbearing age with no contraception method

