#### Intervention and comparator

Mirtazapine will be compared to another antidepressant drug to avoid confusion bias in improving health-related quality of life due to the lone antidepressant effect of mirtazapine. Escitalopram has been chosen as a comparator because it is, like mirtazapine, effective in treating depression in advanced cancer [16], with few medication interactions [17], but no effect on poly-symptomatology is expected.

Both drugs will be used following the usual practice for depression. They will be introduced at a low dose regularly increase at day 7, 14 and 28 depending on the expected benefits from a higher dose and potential dose-dependent side effects. (Table 3).

**Table 3 Tab3:** Doses escalation during the study follow up

		**Starting doses – Day 0**	**Day 7**	**Day 14**	**Day 28**
		Mirtazapine: 15 mg Escitalopram: 10 mg (or 5 mg for patients older than 65)			
Excessive drowsiness (CTCAE grade 1 or rated moderate or severe using the ASEC)			*For patients under 65 in the escitalopram arm: decrease to 5 mg*		
			*For every other patients: Stop the treatment*		
Any severe adverse effect or serious adverse event (CTCAE grade > 3 or rated severe using the l’ASEC)			*Stop the treatment*		
Moderate adverse event (CTCAE grade 2 or rated moderate using the ASEC)			Decrease the dosage (Or treatment stop if already at the lower dosage)		
Mild adverse event (CTCAE grade 1 or rated mild using the ASEC)			No dose adjustment		
No adverse event	Inadequate symptoms’ control (ESAS > 3)		No dose adjustment (or increase the dosage if escitalopram has been started at 5 mg)	Increase the dosage	
	Adequate symptoms’ control (ESAS ≤ 3)		No dose adjustment		

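### Day-14 dose escalation depends on a current ESAS-12F score, but no ESAS-12F is scheduled between inclusion and day 28

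*Protocol article*

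**What the plan says.** Three parts of the protocol article bear on this.

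- **The rule.** Under Follow-up procedure, on day 14 "escalation of dose will be prescribed by the PI if symptoms are still under controlled (the corresponding ESAS12-F subscale rated over 3", with the further condition that ASEC and CTCAE show no limiting side effect. Table 3 (Intervention and comparator) uses the same cut-off. Among patients without an adverse event, the row headed "Inadequate symptoms’ control (ESAS > 3" leads to an increase at day 14, and the row for scores of 3 or less leads to no change. At day 7 the first of these rows reads "No dose adjustment (or increase the dosage if escitalopram has been started at 5 mg".
- **The data.** Table 1 marks the ESAS-12F at inclusion, day 28 and day 56 only. The row "Treatment doses adaptation" is marked at day 14 and, in brackets, at day 7. The text describes the two calls thus: "Patients will be called by a research assistant on days 7 and 14 to screen for side effects using the ASEC scale".
- **Eligibility.** Table 2 requires "Suffering from at least one under-controlled symptom (defined as a score over 3 on the Edmonton Symptom Assessment Scale", for one of seven listed symptoms.

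**The concern.** A titration rule can be followed only if the score it needs is obtained before the decision. Here the rule separates patients whose symptoms have come under control from those whose symptoms have not, yet the schedule shows no symptom rating between inclusion and the day-14 decision.

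Titration is part of the treatment strategy being compared. If the schedule does not supply the score, the rule either falls back on a value that cannot tell these patients apart, or depends on a rating that the protocol does not describe. The trial is open-label and its primary outcome is patient-reported, so undescribed ratings behind dose decisions are best avoided. They could vary between sites, and nothing in the plan guards against variation between arms.

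**Working it through.** No figure of the plan is at stake, so the check sets its parts side by side.

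**Step 1. What is scheduled, from Table 1**

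| Row | Day 0 | Day 7 | Day 14 | Day 28 | Day 56 |
|---|---|---|---|---|---|
| ESAS-12F | yes | no | no | yes | yes |
| ASEC | yes | yes | yes | yes | yes |
| Dose adaptation | yes | in brackets | yes | yes | yes |

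Scheduled ESAS-12F ratings after inclusion and up to the day-14 decision: 0. The next is on day 28, and 28/56 = half of the treatment period has then passed. The text agrees with the table. The calls are for the ASEC; at the day-28 visit, "During this consultation, the patient will fulfil the EORTC QLQ-C30, ESAS -12F, HADS-D, and ASEC questionnaires"; and the ESAS-12F symptom outcomes under Outcomes assessment use baseline, day 28 and day 56.

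**Step 2. What the rule needs, from Table 3 (patients without an adverse event)**

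| Decision | ESAS above 3 | ESAS 3 or less | Does ESAS change the action? |
|---|---|---|---|
| Day 7, escitalopram started at 5 mg | increase | no change | yes |
| Day 7, all others | no change | no change | no |
| Day 14, both arms | increase | no change | yes |

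The missing score therefore matters at day 14 in both arms. At day 7 it matters only for the 5 mg escitalopram starters, whom Table 3 identifies as patients older than 65.

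**Step 3. What the available score can do**

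The only scheduled score before day 14 is the inclusion score. Eligibility requires it to exceed 3 on at least one listed symptom, so every eligible patient meets the inadequate-control condition on at least one symptom. This does not mean that every subscale exceeds 3. The day-14 text refers to the subscale of the symptom concerned, and a symptom that was insufficiently controlled at entry was above 3 at entry by definition. On scheduled data, then, no patient can be classed as adequately controlled at day 14.

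**Step 4. What still separates patients**

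The adverse-event condition works as planned, because the ASEC is collected at both calls. Table 3 allows an increase only when there is no adverse event; a mild event means no change, and worse events mean a reduction or a stop. At day 14 this is the only condition that scheduled data can apply.

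**The case against.** The strongest reply is that the rule speaks of symptoms that are still insufficiently controlled, which implies a current rating, and leaves the prescription to the investigator. Table 1 is an overview in a condensed article, and an ESAS item asked by telephone for titration, without being kept as outcome data, would be compatible with the text. This stands in part. A reader might infer that the investigator must use the inclusion score; nothing says so, and an ad hoc rating is not excluded. But no such rating is described. Table 1 goes instrument by instrument, marks the ASEC at both calls and leaves the ESAS-12F blank, and the text gives the calls the same content. That is a conflict between printed statements, not detail left to the full protocol.

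Other stronger readings are not supported:

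- *All patients would be escalated at day 14, whether or not they respond.* The adverse-event condition still filters them, so 100% meet one of two conditions, not both.
- *Day 7 is affected as day 14 is.* It is affected only in the branch shown in Step 2.
- *The sentence that doses "regularly increase at day 7, 14 and 28 depending on the expected benefits from a higher dose" contradicts Table 3.* The sentence goes on to mention side effects and refers to Table 3 for the rule. It is a loose summary.
- *Ratings would differ by arm, or needless escalation would cause harm.* Both are possible, but the documents contain nothing to show or size either.
- *The primary analysis is undermined.* The day-56 endpoint, the intention-to-treat analysis and the sample size do not use the day-14 score, and the day-28 dose decision has a current ESAS-12F.

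**Conclusion.** The point holds as an internal inconsistency. A stated dosing condition at day 14, in both arms, needs a score that the schedule does not collect; the same is true at day 7 for patients started on escitalopram 5 mg. On scheduled data the adequate-control branch is empty at day 14, and improvement in symptoms cannot alter the dose decision before day 28.

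This rests on two assumptions: that Table 1 is complete for the instruments it lists, and that the Edmonton scale in the eligibility criterion is the ESAS-12F given at inclusion. The effect on the dose actually received, and through it on the outcome, cannot be sized. It depends on what investigators would do in place of the missing score and on how many patients improve by day 14, and the documents give neither.

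**What to change.** Reconcile Table 1, Table 3 and the Follow-up procedure section by one of two routes; the clinical team decides which dosing rule applies.

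1. **Collect the score.** Add the ESAS-12F to the existing day-14 call, and to the day-7 call for the branch that needs it. Mark it in Table 1 and state that the result reaches the investigator before the dose decision. Asking all patients at day 7 would keep the calls alike in both arms. The extra scores can be labelled as titration data, leaving the outcome time points unchanged.
2. **Restate the condition.** Word the day-14 condition, and the day-7 branch, so that they use only what is collected at those contacts.

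The first route costs a few patient-reported questions in calls already planned, plus a schedule amendment. The second costs a wording amendment only. Neither changes the sample size or the primary outcome.

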#### Outcomes assessment

The outcomes will mainly be assessed using patients reported outcome measurements (PROMs) to better reflect the patients’ experience associated with the evaluated treatment. As depressive self-assessment of depressive state might not capture dynamic changes in depressive mood, the depressive mood assessment will rely on a self-assessment, a hetero-assessment and a composite criterion.

The primary outcome will be difference in the health related quality of life, measured at baseline and day 56 using the Global Health Status (GHS) score derived from the EORTC-QLQ-C30 [18–20]. We will consider that a small difference in the GHS score will be between 4 and 8, and a medium difference will be over 8 between baseline and day 56 [21, 22].

The secondary outcomes will include the improvement in the patient’s dynamic experience between baseline and day 56 of the negative experience of symptoms, explored using semi-structured interviews focusing on the experience of symptoms, polymedication and taking antidepressant drugs.

The proportion of symptoms, for each patient, that have been reported as less intense using the ESAS-12F scale between baseline and day 56 if they were reported at baseline, among: depressive mood, pain, nausea, vomiting, loss of appetite, breathlessness, sleep disorders, and anxiety. A lesser degree of intensity will be considered from a 1 point difference [23].

The improvement in the intensity of each symptom using the ESAS-12F subscales between baseline, day 28 and day 56, if they were reported at baseline. A modification in the symptom’s intensity will be considered from a 1 point difference [23].

Any improvement in depressive mood will be assessed using the HADS-D scale and considering a modification in the patient’s mood from a 1.5 points difference between baseline, day 28 and day 56 [24]. We will also use a hetero evaluation scale, the Montgomery-Åsberg Depression Ratting Scale (MADRS) to compare depressive mood between baseline, day 28 and day 56. A difference over 1.9 points will be considered as significant [25]. A composite criterion of both scales’ improvement will also be assessed between baseline, day 28 and day 56 [24, 25].

The proportion of patients having an improvement in the different EORCT-QLQ-C30 functioning scales will be compared between baseline, day 28 and day 56. The following cut-offs will be used for defining significant changes: 3 points for the Cognitive Functioning, 2 points for the Physical functioning, and 6 points for the Emotional Functioning and Role functioning [26, 27]. Financial functioning will not be assessed as the French health care system does not fit with this evaluation (cancer care is free of charge to the patient).

Weight variations will be assessed between baseline, day 28 and day 56.

The use of painkillers will be assessed using the proportion of patients that had stable (± 20%) morphine oral equivalent between baseline, day 28 and day 56. For other symptomatic treatments, the proportion of patients that increased the doses (or had new symptomatic treatment) between baseline, day 28 and day 56 will be assessed.

The security of use will be assessed using the number of new adverse effects reported using the ASEC on day 14, 28 and 56 and compared with baseline. Adverse events will also be recorded and graded using the CTCAE V4.0. The ESAS12-F subscales for drowsiness, fatigue and constipation will be used to compare these symptoms between baseline, day 28 and day 56. A higher degree of intensity will be considered from a 1 point difference [23].

Finally, adherence to medication will be assed using the MARS and Proportion for Days Covered at day 56 [28].

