### Sample Size

Based on an expected standard deviation of 26 in our primary outcome (The Global health Status), and considering a correlation of 0.5 between inclusion and day 56 (corresponding in a standard deviation of the variation of the GHS score of 26 between baseline and day 56), and expecting a moderately clinically significant difference of 8 points between groups, it will be necessary to include 418 participants (bilateral test, alpha risk of 0.05, power of 0.8, attrition 0.2).

Considering the risk of lost to follow-up due to our population global condition, we considered an attrition rate of 20% when calculate the sample size.

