#### Randomization

On the day on inclusion, participants will be randomly assigned to one of the two arms of the study by the ENNOV Clinical software. We will use the minimization method. Due to the important influence on quality of life, the Performance status, and the number of symptoms for which intensity is over 3 will be considered during randomization. The inclusion centre will also be considered.

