### Statistics

The mean Global Health Status (GHS) in our population has been esteemed to 37.5 ± 10.4 [29] or 39 ± 26 [30]. Considering a standard deviation equal to 26 under the hypotheses that (i) the variance of the GHS score at inclusion and at day 56 are equal, and that (ii) the correlation between the score at day 0 and day 56 is equal to 0.5, and expecting a clinically significant change in the GHS of 8 points between day 0 and day 56, we calculated that 167 participants are needed in each group for an 80% study power. Considering the high risk of attrition in our population, we increased by 20% the number of participants needed, resulting in a total number of patients needed to 418 participants.

Analyses will be performed in intention to treat. The intention to treat population will be defined as all patients included in the study, regardless if they are assessed for the primary outcome or not. A modified intention to treat population will be defined as the intention to treat population without participants deceased before the end-point or for whom the primary outcome is missing.

Analyses will be performed using the SAS 9.4 software (SAS Institute Inc., Cary, NC, USA), considering an alpha-risk of 0.5.

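### The primary endpoint and sample size rest on the unadjusted change in GHS; adjusting for baseline GHS would, on the plan's own inputs, raise power from about 80% to about 90% at the same N

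*Protocol article*

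**What the plan says.** The protocol article, Outcomes assessment, defines the endpoint as a within-patient difference: "The primary outcome will be difference in the health related quality of life, measured at baseline and day 56", scored as the GHS of the EORTC QLQ-C30.

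The Sample Size section sizes the trial on the same quantity. It starts from a score SD of 26 ("Based on an expected standard deviation of 26 in our primary outcome") and a correlation of 0.5, "corresponding in a standard deviation of the variation of the GHS score of 26 between baseline and day 56". The target is stated as "expecting a moderately clinically significant difference of 8 points between groups", with "bilateral test, alpha risk of 0.05, power of 0.8, attrition 0.2". The Statistics section repeats the two working hypotheses, that "the variance of the GHS score at inclusion and at day 56 are equal" and that "the correlation between the score at day 0 and day 56 is equal to 0.5". It arrives at 167 per group and 418 in total.

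The Randomization section uses minimisation. Because of their bearing on quality of life, "the Performance status, and the number of symptoms for which intensity is over 3 will be considered during randomization"; centre is the third factor. Baseline GHS is not among them.

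On analysis, the Statistics section gives the populations, the software and an alpha level. It names no test, model or covariates for the primary comparison.

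**The concern.** Under the plan's own assumptions, subtracting baseline gains nothing. With equal variances and a correlation of 0.5, the change has the same SD as the day-56 score alone, and the plan writes this equality down. Using baseline GHS as a covariate instead would remove a quarter of the variance. The sizing takes no account of this.

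Two things are at stake. The first is precision: baseline GHS is collected anyway, and ignoring it leaves the trial at 80% power when the same patients could give about 90%. The second is chance imbalance. Since baseline GHS is not balanced by design, the arms may differ on it at entry. A change score over-corrects for such a difference: through regression to the mean, it favours the arm that starts lower.

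The plan also balances on Performance Status and symptom count because it regards them as prognostic. An analysis that then left them out would not follow from that reasoning.

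**Working it through.** **Inputs** (protocol article, Sample Size and Statistics): score SD σ = 26 at both times; correlation ρ = 0.5; between-group difference δ = 8; two-sided alpha 0.05; power 0.80; attrition 20%; 167 evaluable per group. The Statistics section also prints an alpha of 0.5 and describes the 8 points as a change over time. Only 0.05 and a between-group difference reproduce the stated N, so those are used here.

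**1. Reproducing the plan's figure**

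- SD of change = σ√(2(1 − ρ)) = 26 × √(2 × 0.5) = 26.0.
- n per group = 2(1.960 + 0.842)² × 26² / 8² = 165.8, so 166 by the normal approximation. The noncentral t gives 167 (power 80.05%).
- Attrition: 2 × 167 / 0.8 = 417.5, so 418.

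The published N is therefore the one for an unadjusted two-sample test of change.

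**2. Adjusting for baseline GHS**

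- Residual SD = σ√(1 − ρ²) = 26 × √0.75 = 22.5.
- Variance falls from 676 to 507, a factor of 0.75. In general the factor is (1 + ρ)/2, which is below 1 for every correlation below 1.

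**3. Power with 167 per group**, as Φ(δ / (SD × √(2/167)) − 1.96):

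- Change: standard error 26 × 0.1094 = 2.85; 8/2.85 = 2.81; power 80.3% (80.1% by the noncentral t).
- Adjusted: standard error 22.5 × 0.1094 = 2.46; 8/2.46 = 3.25; power 90.1% (89.9% by the noncentral t).
- Adjusted n for 80% power: 2(1.960 + 0.842)² × 507 / 64 = 124.4, so 125 per group by the normal approximation, against 166 on the same basis for change.

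**4. Sensitivity to the correlation**, with score SD fixed at 26, 167 per group and the normal approximation:

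| Correlation | Change | Baseline-adjusted |
|---|---|---|
| 0.3 | 66% | 84% |
| 0.4 | 73% | 87% |
| 0.5 | 80% | 90% |
| 0.6 | 88% | 94% |
| 0.7 | 95% | 98% |

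If instead the SD of change is held at 26 whatever the correlation, change stays at 80% and the adjusted analysis gives 94% at 0.3 and 86% at 0.7.

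**5. Chance imbalance in baseline GHS**

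- Standard error of the baseline difference = 26 × √(2/167) = 2.8 points.
- The day-56 score regresses on baseline with slope 0.5, whereas the change score subtracts baseline with slope 1. A one-standard-error imbalance therefore shifts the change contrast by (1 − 0.5) × 2.8 = 1.4 points, or 1.4/8 = 18% of the target difference.

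**6. Minimisation factors**

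The documents do not say how much day-56 variance these explain, so no gain from them is counted. Purely as an assumption, a further 2%, 5% or 10% would give 90.8%, 91.9% or 93.7% power.

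**The case against.** The strongest objection is that the article never states an unadjusted analysis. The Outcomes assessment section says what is measured, not how it is modelled. A change endpoint does not exclude adjustment: a linear model of change with baseline as a covariate gives the same treatment estimate and standard error as the same model of the day-56 score, because only the baseline coefficient moves, by 1. Sizing without credit for covariates is also a common conservative choice and commits the trial to nothing. Model and covariates are ordinary content of an analysis plan, which is not shown here.

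All of this stands. A reader might infer that the plan commits to a raw change-score test, that its standard errors will be too wide, or that the trial is underpowered or biased. The documents do not support these readings. No model is named. The change-score design meets its own 80% target. Under randomisation its contrast is unbiased over repetitions, and the imbalance effect in step 5 is conditional on the trial that happens to be drawn. Silence about the minimisation factors is not an error either.

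What remains is narrower. The endpoint and the arithmetic reflect one method only, the unadjusted comparison of change, and on the plan's own inputs a better one is available at the same N.

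**Conclusion.** The point holds as an efficiency gain to secure in advance, not as an error in the plan. At the plan's inputs, adjusting for baseline GHS reduces the residual SD from 26 to 22.5 and raises power from about 80% to about 90% with the same 418 randomised patients. It also removes the conditional effect of a chance baseline imbalance.

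The 90% rests on a correlation of 0.5, equal variances at the two times and 167 evaluable patients per group after 20% attrition. The plan itself labels the first two as hypotheses. With score SD fixed, the gain is largest where the design is most fragile: if the correlation is below 0.5, the unadjusted comparison falls under 80% while the adjusted one stays above it at 0.3 and 0.4. The 90% comes from baseline GHS alone. If the analysis plan already adjusts for baseline, all that remains is to say so beside the endpoint definition.

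**What to change.** Unless the analysis plan already does so, specify the primary analysis as a linear model of day-56 GHS (or, equivalently, of change) with terms for arm, baseline GHS, Performance Status, number of symptoms above 3, and centre, with centre random or small centres pooled. Report the adjusted mean difference between arms with its 95% confidence interval. Keep N at 418 and let the added precision serve as a margin against a lower correlation or higher dropout. Keep the unadjusted comparison of change as a supportive analysis.

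The cost is wording in the protocol or analysis plan. Table 1 shows the QLQ-C30, the ESAS-12F and Performance Status collected at the inclusion visit, and centre is known at randomisation. The between-group quantity being estimated does not change. Because the trial is open-label, the model should be fixed before any comparison by arm, so that the choice of covariates cannot be questioned afterwards.

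### The QLQ-C30 functioning outcomes are stated only as proportions of patients improved, which discards information that a baseline-adjusted mean comparison would keep at no extra data cost

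*Protocol article*

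**What the plan says.** The Objectives section of the protocol article lists improvement in functional capacities at day 56 among the secondary objectives. Outcomes assessment then fixes how this is measured: "The proportion of patients having an improvement in the different EORCT-QLQ-C30 functioning scales will be compared between baseline, day 28 and day 56". A patient counts as improved at a change of "3 points for the Cognitive Functioning, 2 points for the Physical functioning, and 6 points for the Emotional Functioning and Role functioning". No analysis of the functioning scores on their original scale is described.

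The only figures for spread and effect concern the primary outcome, the Global Health Status (GHS) of the same questionnaire. Sample Size gives a "standard deviation of the variation of the GHS score of 26" and an expected between-group difference of 8 points. Outcomes assessment says that "a small difference in the GHS score will be between 4 and 8". No SD, expected effect or power is given for any functioning scale.

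**The concern.** Each functioning score is reduced to a yes/no label per patient. A patient who gains 3 points and one who gains 40 count the same on physical functioning, and so do a patient who loses 40 and one who gains 1. The between-arm test then works with less information than the scores hold and can miss a difference that a comparison of means would show.

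The cut-offs raise a second, separate issue. Against a change SD of 26, a cut-off of 2 points is 2/26 = 0.08 SD and one of 3 points is 3/26 = 0.12 SD. Patients either side of such a line hardly differ, so a large share of each arm will be called improved even when the average change is nil. The percentage is then hard to interpret clinically.

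At stake is the precision and readability of a secondary result that supports the quality-of-life hypothesis. The primary GHS result is not affected.

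**Working it through.** **Inputs.** From Sample Size and Statistics, all for GHS: score SD 26 at both times, correlation 0.5, difference 8 points, 167 evaluable per arm, and "bilateral test, alpha risk of 0.05, power of 0.8, attrition 0.2". Statistics also says "considering an alpha-risk of 0.5"; this conflicts with Sample Size, is a separate matter, and is not used here. Cut-offs of 2, 3 and 6 points come from Outcomes assessment. Applying the GHS SD and difference to the functioning scales is an assumption, so the SD is varied below.

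**1. Reproduce the plan's own figure.**
- SD of change = √(26² + 26² − 2 × 0.5 × 26 × 26) = 26.
- n per arm = 2 × [26 × (1.960 + 0.842) / 8]² = 166 by the normal approximation. The t test needs 167 (power 80.05%).
- Total = 2 × 167 / 0.8 = 417.5, so 418. The stated 167 and 418 are reproduced.

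**2. Power for means, 167 per arm, 8 points.**
- Mean change: SE = 26 × √(2/167) = 2.845. Power = Φ(8/2.845 − 1.960) = Φ(0.852) = 80.3%.
- Mean adjusted for baseline: residual SD = 26 × √(1 − 0.5²) = 22.52, SE = 2.464. Power = Φ(8/2.464 − 1.960) = 90.1%.

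**3. Power for proportions, same data.** With normally distributed change and zero mean change in the control arm, p0 = 1 − Φ(c/26) and p1 = 1 − Φ((c − 8)/26). Power = Φ[(p1 − p0 − 1.960 × SE0)/SE1], where SE0 is pooled and SE1 unpooled.

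| Cut-off c | p0 | p1 | Power |
|---|---|---|---|
| 2 | 46.9% | 59.1% | 60.8% |
| 3 | 45.4% | 57.6% | 60.9% |
| 6 | 40.9% | 53.1% | 60.8% |

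For c = 2: p1 − p0 = 0.1219 before rounding, SE0 = 0.0546, SE1 = 0.0542, giving Φ(0.274) = 60.8%. Reaching 80% with proportions would need 262 evaluable per arm, which is 262/167 = 1.57 times as many. Moving the control mean by 8 points either way leaves power at 58.5% to 60.0%.

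**4. Does the size of the cut-off drive the loss?** Same model, other cut-offs: 60.9% at 4 points, 60.0% at 10, 58.0% at 15, 54.9% at 20, 49.7% at 26. The stated cut-offs sit at or near the maximum, and larger ones do worse. The loss comes from dichotomising.

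**5. Other SDs, 8 points and 167 per arm.** The last column is the share passing the cut-offs of 2, 3 and 6 points when mean change is zero.

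| SD of change | Power, mean change | Power, proportions | Share passing 2 / 3 / 6 |
|---|---|---|---|
| 26 | 80% | 61% | 47% / 45% / 41% |
| 20 | 95% | 83% | 46% / 44% / 38% |
| 15 | 99.8% | 97% | 45% / 42% / 34% |
| 10.4 | near 100% | near 100% | 42% / 39% / 28% |

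The value 10.4 is the other GHS SD cited in Statistics; 15 and 20 are assumed intermediate values. If the difference is instead rescaled so that the mean comparison always has 80% power, proportions have 57.7% to 60.6% for SDs from 10.4 to 30. So the relative loss is stable, but the absolute loss for a fixed 8 points is not.

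**The case against.** The strongest reply is that any responder analysis is less efficient than a comparison of means, so this is not an error peculiar to this trial. The functioning outcomes are secondary and were never powered, and an analysis plan that is not shown may add mean scores. All of that is fair and sets the weight of the point. It does not remove it, because the article states the proportion as the method rather than leaving the method open.

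Four stronger readings are tempting, and the document does not support them.
- *The low cut-offs cause the power loss.* They do not: power is about 61% at 2, 3 and 6 points alike and falls at higher cut-offs.
- *The comparison is biased.* It is not. With randomisation, chance improvers are expected equally in both arms, so the between-arm test stays valid.
- *Nearly half of patients with no true change are labelled improved.* SD 26 describes observed change across patients and includes real gains and losses. The calculation therefore describes a group whose mean change is zero. Nor does nearly half fit emotional and role functioning, at 41% for SD 26 and 28% for SD 10.4.
- *The cut-offs are wrong because they lie below the small range for GHS.* That range is for another scale, the functioning cut-offs cite their own sources, and 6 points lies within 4 to 8. An argument from the smallest possible step on each scale would need scoring rules that the document does not give.

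**Conclusion.** The point holds as a cheap improvement. The article commits the functioning outcomes to a proportion improved and describes no analysis that keeps the score. On GHS values borrowed as an assumption, that costs about 19 percentage points of power against mean change (80.3 − 60.8 = 19.5) and about 29 against a baseline-adjusted mean (90.1 − 60.8 = 29.3). At SD 20 the loss against mean change is about 12 points (95 − 83), and at SD 15 or below it is negligible for an 8-point difference. A reader should not infer that the trial has 61% power for functioning, since no SD or effect for these scales is stated.

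Separately, the percentages will be hard to interpret. With zero mean change, between 28% and 47% of patients would count as improved, depending on the cut-off and on an SD between 10.4 and 26. The calculations assume normally distributed change and equal arms of 167.

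**What to change.** For each functioning scale, state the analysis as the between-arm difference in mean score at day 28 and day 56, adjusted for the baseline score, with a confidence interval. Keep the proportions improved at the present cut-offs, if wanted, as a descriptive display beside it.

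The cost is wording only: Table 1 already schedules the questionnaire at inclusion, day 28 and day 56, so no new data, visits or patients are needed. The small downside is that the main functioning result becomes a mean difference and not a percentage.
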